## 2.8. INTERIM ANALYSES

No interim analyses comparing study outcomes between the allocated groups were conducted.

## 2.9. DATA COLLECTION

Participants in the trial will undergo a face-to-face assessment, two appointments (pre and post-randomisation) and swab collection on Day 1. They are required to complete online or paper trial diaries at baseline (Day 1, pre-randomisation) and then from Day 1 (post-randomisation) until symptom resolution or 28 days post-randomisation, whichever comes first. At 2 months, there will

be follow-up with a questionnaire on participants' beliefs. Data on any primary care consultations and hospital admission for RTIs or antiviral prescribing up to 28 days will be collected from primary care medical records at 2 months, as well as primary consultation for RTIs between Day 29 or up to 6 months will be collected at 6 months. The Supplementary Table at the end of this document shows the summary of the assessment schedule and outcomes measured at each time point.

## 2.10. OUTCOME MEASURES

All outcome data will be obtained from case report forms, participants' Trial diary and questionnaires of participants' and Clinicians' views.

### 2.10.1. CLINICAL PRIMARY OUTCOMES

| Primary Outcome        | Type   | Outcome detail                                                                                                                                                                 |
|------------------------|--------|--------------------------------------------------------------------------------------------------------------------------------------------------------------------------------|
| Antibiotic prescribing | Binary | The primary outcome is whether an antibiotic is prescribed (included delayed prescribing) for a RTI on day 1. Study clinician report on Appointment 2 case report form. |

The study clinician will collect the following data onto the **study case report form**: eligibility criteria, consultation format, signs and clinical measurements at presentation, diagnosis, medical history, previous prescription of antibiotic for current episode of RTI, POCT result, details of any prescription at appointment two (= primary outcome).

### 2.10.2. CLINICAL SECONDARY OUTCOMES

**Participant-completed symptom diaries** at baseline (day 1, pre-randomisation) and for 28 days afterwards (first post-randomisation completion on day 1 after appointment 2). Ten symptoms were completed by all participants: blocked nose, fever, shortness of breath, phlegm, wheeze, eating or drinking less than normal, disturbed sleep, ear pain and change in voice. Those age 16+ years completed four further symptoms: sore throat, muscle facial or head aching or pain, sweats or chills, and unable to do usual activities e.g. work school childcare etc. Those age under 16 years completed one additional item: child not themselves or more clingy than usual. Each item was responded to using the following seven-point scale:

- 0 = Normal/not affected
- 1 = Very little problem
- 2 = Slight problem
- 3 = Moderately bad
- 4 = Bad
- 5 = Very bad
- 6 = As bad as it could be

Participants are instructed to stop completing the diary once they have two consecutive days for which all symptoms are rated at zero, or once 28 days have been completed.

For any diary days that have been partially completed, with at least one symptom completed, symptoms left blank will assumed to be scored as zero (i.e. the symptom is completely resolved). Any days with no symptoms rated will be considered as missing data.

In addition participants were asked to record in the daily diaries if they were taking an antibiotic, which one, and how many doses were taken each day.

The following measures were derived from participant-completed symptom diaries:

| Diary measures                                                                         | Type       | Outcome detail                                                                                                                                                                                                                                                                                                                               |
|----------------------------------------------------------------------------------------|------------|----------------------------------------------------------------------------------------------------------------------------------------------------------------------------------------------------------------------------------------------------------------------------------------------------------------------------------------------|
| Mean symptom severity on days 2 to 4
(KEY SECONDARY OUTCOME)                        | Continuous | Each day's responses will be converted to a mean score = sum of responses divided by the listed number of symptoms.                                                                                                                                                                                                                          |
| Duration of moderately bad (or worse) symptoms                                         | Ordinal    | Longest continuous spell (in days) with one or more symptoms rated $\geq 3$ , concluding with two days where all symptoms are rated $< 3$ .                                                                                                                                                                                                  |
| Number of days to return to usual activities (adult participants $\geq 16$ years only) | Ordinal    | For participants with "Unable to do usual activities" rated $\geq 3$ at baseline, the number of consecutive days that item is rated $\geq 3$ , followed by two days where it is rated $< 3$ . For participants with "Unable to do usual activities" rated as $< 3$ at baseline, their duration will be zero.                                 |
| Number of days to return to usual activities (child participants $< 16$ years only)    | Ordinal    | For participants with "Child not themselves / more clingy than usual" rated $\geq 3$ at baseline, the number of consecutive days that item is rated $\geq 3$ , followed by two days where it is rated $< 3$ . For participants with "Child not themselves / more clingy than usual" rated as $< 3$ at baseline, their duration will be zero. |
| Overall symptom duration                                                               | Ordinal    | The number of consecutive days one or more symptoms are rated $> 0$ , concluding with two days where all symptoms are rated 0.                                                                                                                                                                                                               |
| New or worsening symptoms                                                              | Binary     | Over days 2 to 28, the participant sees one or more symptoms increase to a score of $\geq 3$ , and is scored $\geq 3$ for at least one of the subsequent two days.                                                                                                                                                                           |
| Consumption of antibiotics                                                             | Count      | Number of days on which antibiotics are consumed on days 1 to 28.                                                                                                                                                                                                                                                                            |
| Counsumption of antivirals                                                             | Count      | Number of days on which antivirals are consumed on days 1 to 28.                                                                                                                                                                                                                                                                             |

**Participant views and study clinician views** were collected using the following eight questions at the indicated time points (P: participant, C: clinician). Given wording was for clinicians, with the same questions asked of participants but with wording adapted. The response options were as follows:

- 1 Strongly disagree
- 2 Disagree
- 3 Neither agree or disagree
- 4 Agree
- 5 Strongly agree

|     |                                                                                                                                | First contact | Appt 1 | End appt 1 | Allocation & test result | End appt 2 | 2 mths |
|-----|--------------------------------------------------------------------------------------------------------------------------------|---------------|--------|------------|--------------------------|------------|--------|
| [1] | I believe an antibiotic is needed to treat the patient's illness                                                               | P             | C      | P          | C                        | P          |        |
| [2] | I believe the patient's illness will improve faster                                                                            | P             | C      | P          | C                        | P          |        |
| [3] | I believe the patient's illness will be less severe if I prescribe an antibiotic                                               | P             | C      | P          | C                        | P          |        |
| [4] | The point-of-care test would help in making the right decision about whether the patient needs antibiotics                     |               | C      | P          |                          |            |        |
| [5] | The point-of-care test would have helped / has helped in making the right decision about whether the patient needs antibiotics |               |        |            | C                        | P          |        |
| [6] | I am confident that the patient will believe they are getting the right treatment                                              |               | C      | P          | C                        |            |        |
| [7] | If a patient has a similar infection in future I am likely to prescribe them antibiotics                                       |               |        |            | C                        |            | P      |
| [8] | If a patient has a similar illness in future I would like to use the point-of-care test                                        |               |        |            | C                        |            | P      |

Participants' **primary care medical records** will be reviewed at 2 and after 6 months to capture information on prescribing, consultations and hospital admissions.

| Medical records review                  | Type | Outcome detail                                                                                    |
|------------------------------------------------|-------------|----------------------------------------------------------------------------------------------------------|
| Antibiotic prescriptions after appointment two | Binary      | One or more antibiotic prescriptions after appointment two and within 28 days                            |
| Antiviral prescriptions after appointment two  | Binary      | One or more antiviral prescriptions after appointment two and within 28 days                             |
| Number of respiratory infection consultations  | Count       | The number of respiratory infection consultations within 28 days and after 28 days but within 6 months.  |
| Hospital admissions for respiratory infections | Binary      | One or more hospital admissions for a respiratory infection within 28 days, from medical records review. |

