| 8. The quantity and timing of antibiotic and antiviral prescribing after Appointment Two and ≤28 days                                                                                   | Name, strength, frequency and quantity of antibiotics and antivirals prescribed after Appointment Two and ≤28 days                                                                                                                                                                                                                                                                                                                                                   | Retrospective collection from PCMR at least 2 months after recruitment |
| 9. Number of days on which antibiotics and antivirals are consumed ≤28 days                                                                                                             | Name of antibiotic and antiviral, and number of times per day the medicine was consumed                                                                                                                                                                                                                                                                                                                                                                              | Trial Diary  completed daily by participant               |

| Objective                                                                                                                       | Outcome Measure                                                                           | Source and published reference (where applicable)                  |
|---------------------------------------------------------------------------------------------------------------------------------|-------------------------------------------------------------------------------------------|--------------------------------------------------------------------|
| 10. Participant (or parent/carer if the participant is <16 years) intention to consult for similar future illnesses at 2 months | See Appendix 1 (Participant views questions 7 and 8)                                      | Questionnaire completed by participant 2 months post-randomisation |

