### **6.9 Follow-Up**

The Trial Diary will be completed daily by the participant until their symptoms resolve (defined as all symptoms being rated zero for two days in a row) or up to day 28, whichever comes first. The central trial team will contact participants regularly via email, text or phone to support completion of the Trial Diary. Completed paper versions of the Trial Diary should be returned to BTC. Participants will be advised that if their symptoms have not resolved by Day 28, or if they have any concerns before Day 28, they should contact their GP practice for further advice.

Participants (or parent/carer if the participant is <16 years) will be followed-up with a questionnaire at 2 months post-randomisation which will collect beliefs and intention to consult for similar future illnesses (see Appendix 1, Participant Views questions 6 and 7). Up to two reminders will be sent for cases where the questionnaires are not returned. Questionnaires may be completed with the participants over the phone, and the data entered by the central trials team, if required. In addition, data on any further GP consultations for RTIs will be collected from their PCMR at 2- and 6- months after randomisation. For those participants randomised in the later stages of Summer 2, there will be a shorter follow-up period to ensure that all follow-up is completed 2 months after recruitment has finished.

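### The 28-day count of antibiotic and antiviral days comes only from a diary that closes at symptom resolution, so intake after closure is not recorded

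*Combined protocol and SAP*

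**What the plan says.** **The outcome.** Objective 9 in protocol Table 1 is "Number of days on which antibiotics and antivirals are consumed ≤28 days". The data behind it are "Name of antibiotic and antiviral, and number of times per day the medicine was consumed", and the Trial Diary is the only source listed. SAP 2.10.2 places both medicines among the diary-derived measures, typed as counts: "Number of days on which antibiotics are consumed on days 1 to 28" and "Number of days on which antivirals are consumed on days 1 to 28".

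**The stopping rule.** Protocol 6.9 has the diary "completed daily by the participant until their symptoms resolve (defined as all symptoms being rated zero for two days in a row"; Day 28 is the latest end. Footnote C to protocol Table 5 agrees. SAP 2.10.2 says: "Participants are instructed to stop completing the diary once they have two consecutive days for which all symptoms are rated at zero".

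**Other sources.** The medical record review at 2 months (protocol Table 5, footnote D) collects consultations, admissions and prescribing up to Day 28. The 2 Month Questionnaire (protocol 6.9 and Appendix 1) collects beliefs and intentions. Neither asks what was taken.

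**Reporting.** The shell of SAP Table 4 shows the number and percentage of patients consuming any antibiotic, or any antiviral, from day 1 to 28. No SAP shell shows the day count.

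**The concern.** After two all-zero days it is reasonable to presume that symptoms stay at zero. The same presumption fails for medicines. A course can run on after symptoms have gone, a delayed prescription can be started late, and a relapse can lead to a new course. None of those days has a diary page.

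The quantity collected is therefore days of intake while the diary was open, not days of intake to Day 28. The end of that window is set by recovery, which happens after randomisation. If recovery speed differed between the groups, recorded days could differ even with identical intake.

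The SAP also leaves the handling of closed days open. Its missing-day rule in 2.10.2 is written for days without symptom ratings. It does not say whether days after closure count as zero intake or as missing, so two analysts could produce different counts from the same data.

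**Working it through.** **1. The plan's own figures.** None is stated for this outcome. The planned sample sizes reproduce: 244 per group for 60% v 45% at 90% power with continuity correction; 488/0.95 = 513.7, so 514; 514 × 0.8/2 = 205.6, so 206. None depends on consumption.

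**2. The documents side by side.**

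| Element | Window | Records intake? |
|---|---|---|
| Outcome definition (protocol Table 1, SAP 2.10.2) | to Day 28 | required |
| Trial Diary | to the second all-zero day, or Day 28 | yes, while open |
| Medical record review | to Day 28 | no, prescribing only |
| 2 Month Questionnaire | 2 months | no, beliefs and intentions |

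Nothing in either document keeps the medicine item open after closure or reopens the diary on relapse.

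**3. What one participant's diary captures.** Let s be the first day of the course, L its length and q the last diary day (the second all-zero day). Then

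recorded days = max(0, min(q, s + L − 1) − s + 1).

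The values below are assumed.

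| s | L | q | Recorded | Lost |
|---|---|---|---|---|
| 1 | 5 | 4 | 4 | 1 |
| 1 | 7 | 4 | 4 | 3 |
| 1 | 10 | 4 | 4 | 6 |
| 1 | 7 | 7 | 7 | 0 |
| 1 | 10 | 7 | 7 | 3 |
| 3 | 7 | 5 | 3 | 4 |
| 14 | 7 | 12 or earlier | 0 | 7 |

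A course that begins while the diary is open is shortened, not erased. Only the last row is missed completely, and if that is the participant's only course, he or she would also count as a non-consumer in SAP Table 4.

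**4. Average loss among users.** Assumptions: the last symptomatic day is lognormal with log SD 0.6, rounded, with a minimum of 1. The diary closes two days later or on Day 28, and every course is taken in full.

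| Course | Days lost at median recovery 5 / 7 / 10 days |
|---|---|
| 5 days from Day 1 | 3% / 1% / 0.2% |
| 7 days from Day 1 | 12% / 6% / 2% |
| 7 days from Day 3 | 30% / 17% / 8% |
| 10 days from Day 1 | 28% / 17% / 9% |

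For the 7-day course from Day 1, the share of users cut short is 43%, 23% and 9%.

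**5. Effect on a between-group difference, if the loss is equal in both groups.** Take the planning rates of 60% and 45% as if everyone prescribed took seven days from Day 1. Mean days are 0.60 × 7 = 4.20 and 0.45 × 7 = 3.15, a difference of 1.05. Proportional losses of 12.2%, 5.7% and 2.0% shrink this by 0.13, 0.06 and 0.02 days per participant. For the 10-day course the difference is 0.15 × 10 = 1.50, and a 28.4% loss removes 0.43. For the Day 3 start, 1.05 × 0.298 = 0.31. The planning rates are prescribing rates that include delayed prescriptions, so this shows scale only.

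**6. Effect on SAP Table 4.** In the model of step 4 the diary never closes before Day 3. Every course started by Day 3 therefore has at least one recorded day, and none of the losses in steps 4 and 5 changes any consumption. That measure changes only for participants whose first dose falls after closure. The documents give no basis for estimating how many there will be.

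**The case against.** The strongest reply is that the tables planned for the results paper report any consumption, not days. Cutting short a course already recorded does not alter that, so the simulated losses do not touch the reported result. This is correct as far as it goes. But the count is still the defined outcome in protocol Table 1 and SAP 2.10.2, so the plan contains two versions that need reconciling.

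Second, later courses are not invisible. The record review captures the name, strength, frequency and quantity of antibiotics and antivirals prescribed after Appointment Two, and the SAP analyses those prescriptions as separate outcomes. This also stands. What is missing is whether, and for how long, the medicine was taken. With delayed prescribing in scope, that is not the same as being prescribed.

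Third, the illustration may be pessimistic. With a median of 5 days, about 28% of participants would have their last symptomatic day by Day 3. That sits awkwardly with the planning mean severity of 2.3 (SD 1.5) over days 2 to 4, and this scenario gives the largest losses.

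Fourth, the SAP describes the diary partly in the past tense and already refers to two practices with low completion, so a change to data collection may come too late for most participants. That affects which part of the fix is usable, not whether the mismatch exists.

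A reader might also infer that the plan understates the test's effect on antibiotic exposure, because more control participants are expected to be prescribed. Or the reader might infer that it flatters the test, because late courses may be commoner where fewer were treated at first. These pull in opposite directions. The documents supply neither recovery times nor consumption by group, so no net direction can be claimed.

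**Conclusion.** The mismatch is real and can be read directly from the documents. The count of antibiotic and antiviral days to Day 28 is taken only from a diary that may close well before Day 28, and no other source records intake. The tail of a course that outlasts symptoms is lost, and a course first taken after closure is missed as consumption. The undercount depends on a post-randomisation outcome.

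Its size is not known. Under the assumed recovery times and course lengths it ranges from 0.2% to 30% of antibiotic days, and it is most sensitive to course length, start day and speed of recovery. Any between-arm bias cannot be sized or signed.

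It would go too far to say that courses outlasting symptoms go unrecorded, or that relapse treatment leaves no trace. The first are recorded up to closure, and primary care prescriptions after Appointment Two are in the record review. SAP Table 4 is exposed only to courses first taken after closure. This is a secondary outcome; the primary outcome, key secondary outcome and sample size stand. The point deserves correction because the remedy is cheap.

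**What to change.** **Data collection.** Amend protocol 6.9 so that only the symptom items close at two all-zero days. At closure, ask whether an antibiotic or antiviral is still being taken, which one, and its finish date. Add one item to the existing 2 Month Questionnaire on any later intake up to Day 28. The documents name no Day 28 contact, so the questionnaire is the firmer place. A separate stopping point within the diary has a precedent: footnote C to protocol Table 5 runs the EQ-5D to the end of the week in which symptoms resolve.

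**SAP, for participants already past closure.**
- Define the outcome as days of intake while the diary was open.
- State that days after closure are not counted as zero intake.
- Add a sensitivity analysis that completes courses still open at closure. Use the prescription details on the Appointment Two form, if they include quantity (SAP 2.10.1 does not say), and those in the medical record. State that this assumes the course was taken as prescribed.
- Reconcile the count in SAP 2.10.2 with the any-consumption rows in SAP Table 4, either by adding the count to the shell or by naming the binary measure as the outcome. Note that the binary measure misses courses first taken after closure.

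**Cost.** Two or three questions in existing instruments and a few lines of SAP text. Recovered participants carry a slight extra burden, and a recalled finish date is less exact than daily recording.
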